## LIST OF ABBREVIATIONS AND RELEVANT DEFINITIONS

|                |                                                                                                                                                                                                                                                                                                                                                  |
|----------------|--------------------------------------------------------------------------------------------------------------------------------------------------------------------------------------------------------------------------------------------------------------------------------------------------------------------------------------------------|
| ABR     | General Assessment and Registration form (ABR form), the application form that is required for submission to the accredited Ethics Committee; in Dutch: Algemeen Beoordelings- en Registratieformulier (ABR-formulier)                                                                                                                    |
| AE      | Adverse Event                                                                                                                                                                                                                                                                                                                             |
| AR      | Adverse Reaction                                                                                                                                                                                                                                                                                                                          |
| BMI     | Body Mass Index                                                                                                                                                                                                                                                                                                                           |
| CA      | Competent Authority                                                                                                                                                                                                                                                                                                                       |
| CAA     | Circulating Anodic Antigen                                                                                                                                                                                                                                                                                                                |
| CCMO    | Central Committee on Research Involving Human Subjects; in Dutch: Centrale Commissie Mensgebonden Onderzoek                                                                                                                                                                                                                               |
| CV      | Curriculum Vitae                                                                                                                                                                                                                                                                                                                          |
| EU      | European Union                                                                                                                                                                                                                                                                                                                            |
| GCP     | Good Clinical Practice                                                                                                                                                                                                                                                                                                                    |
| HBV     | Hepatitis B Virus                                                                                                                                                                                                                                                                                                                         |
| HCV     | Hepatitis C Virus                                                                                                                                                                                                                                                                                                                         |
| HIV     | Human Immunodeficiency Virus                                                                                                                                                                                                                                                                                                              |
| IB      | Investigator's Brochure                                                                                                                                                                                                                                                                                                                   |
| IC      | Informed Consent                                                                                                                                                                                                                                                                                                                          |
| LUMC    | Leiden University Medical Center                                                                                                                                                                                                                                                                                                          |
| METC    | Medical research ethics committee (MREC); in Dutch: medisch-ethische toetsingscommissie (METC)                                                                                                                                                                                                                                            |
| PD      | Product Dossier                                                                                                                                                                                                                                                                                                                           |
| PZQ     | Praziquantel                                                                                                                                                                                                                                                                                                                              |
| (S)AE   | (Serious) Adverse Event                                                                                                                                                                                                                                                                                                                   |
| SM      | Schistosoma mansoni                                                                                                                                                                                                                                                                                                                |
| SMC     | Safety monitoring committee                                                                                                                                                                                                                                                                                                               |
| Sponsor | The sponsor is the party that commissions the organisation or performance of the research, for example a pharmaceutical company, academic hospital, scientific organisation or investigator. A party that provides funding for a study but does not commission it is not regarded as the sponsor, but referred to as a subsidising party. |
| SUSAR   | Suspected Unexpected Serious Adverse Reaction                                                                                                                                                                                                                                                                                             |
| WMO     | Medical Research Involving Human Subjects Act; in Dutch: Wet Medisch-wetenschappelijk Onderzoek met Mensen                                                                                                                                                                                                                                |

## SUMMARY

**Rationale:** Schistosomiasis is a parasitic disease of global importance, for which no vaccine exists. Vaccine candidates are tested for efficacy in large-scale Phase 2 and 3 field trials in *Schistosoma*-endemic areas, where the endpoint is usually the incidence of infection or disease following natural exposure. Such trials therefore require long duration and/or large population sizes in order to obtain a good estimate of the effect size. Conducting controlled, experimental infection studies have been shown to eliminate several drawbacks of the traditional proof-of-efficacy approach. Previously, we have established a male-only controlled human *Schistosoma mansoni* infection model, that proved to be safe and well-tolerated in healthy *Schistosoma*-naïve healthy volunteers. In this study we aim to develop a female-only controlled human *Schistosoma mansoni* infection model that can be used to provide early proof-of-concept data on candidate schistosomiasis vaccines and serve as a platform to study schistosome immune responses. This is of particular relevance as one of the developed schistosomiasis vaccine candidate's target antigens is preferentially expressed on female schistosomes.

### Objective:

Primary Objective:

- To investigate the safety, tolerability and attack rate of female *Schistosoma mansoni* cercariae in healthy Schistosome-naïve volunteers

Exploratory Objectives:

- To investigate the kinetics of circulating anodic antigen (CAA) after infection with female *Schistosoma mansoni* cercariae in healthy Schistosome-naïve volunteers
- To investigate immunological, metabolic and microbiome changes after infection with *Schistosoma mansoni* female cercariae
- To explore potential differences in CAA kinetics and immunological responses after infection with male or female *Schistosoma mansoni* cercariae

**Study design:** Open label, dose escalation intervention study with adaptive design

**Study population:** Healthy human volunteers, 18-45 years old

**Intervention:** Groups of 3 or 7 volunteers will be exposed to female cercariae. Depending on the outcome of infection and safety data, the dose will be escalated or additional volunteers will be exposed to the same number of cercariae. Volunteers will visit the clinical trial centre weekly after infection to record adverse events.

### Main study parameters/endpoints:

Main study parameter/endpoint:

- Frequency and severity of adverse events after controlled human *Schistosoma mansoni* infection with female cercariae

- The number of female cercariae at which 100% volunteers show detectable *Schistosoma mansoni* circulating anodic antigen

Other study parameters/endpoints:

- Time to positive serum and urine CAA test
- Comparison of the peak serum CAA concentration in different dose groups
- Humoral (antibody) response directed against *Sm* antigens
- Cellular responses directed against *Sm* antigens
- Changes in microbiome after controlled human *Schistosoma mansoni* infection with female *Sm* cercariae

**Nature and extent of the burden and risks associated with participation, benefit and group relatedness:** Volunteers will be requested to visit the trial centre on a weekly basis for 16 weeks. After this bi-weekly visits will follow until week 20. Final follow up visit will be after one year. Blood and urine sampling will take place at every visit. Nasosorption sampling is performed during the first eight weeks. They will keep a diary to record adverse events during 20 weeks. Volunteers will be dermally exposed to female cercariae once. They may experience adverse events, related to acute schistosomiasis syndrome with fatigue, malaise, and fever. At 8 weeks and 12 weeks after infection, they will be treated with praziquantel to cure the *Schistosoma* infection. Praziquantel is known to potentially give fatigue, gastrointestinal side effects, and dizziness. There is no benefit to participation in the trial.

## 1. INTRODUCTION AND RATIONALE

Schistosomes are parasitic helminths of the order Trematoda that are transmitted through snails in (sub)tropical areas. Current estimates suggest that 252 million people are infected with schistosomes [1], with approximately two-thirds of the cases caused by *Schistosoma haematobium* (the cause of urogenital schistosomiasis), one-third caused by *Schistosoma mansoni* (the cause of intestinal schistosomiasis) and approximately one percent caused by *Schistosoma japonicum* and *S. mekongi* (intestinal schistosomiasis). Schistosomiasis together with hookworm infection and leishmaniasis rank as the leading neglected tropical diseases in terms of disability-adjusted life years [2]. More than 90% of the schistosomiasis cases are found in Africa (*S. haematobium* and *S. mansoni*), with the remainder of cases caused by *S. mansoni* in Brazil and Latin America. *S. japonicum* and *mekongi* are endemic in areas in South-East Asia. Endemicity of *Schistosoma* is focal, and mainly related to the presence of fresh water snails of the genus *Biomphalaria*. Depending on the presence of the snail, schistosomiasis can spread to subtropical areas such as the island of Corsica in Europe.

Within the snail, parasites reproduce asexually and are released as infective larval swimming schistosomes, known as cercaria. The cercariae enter the skin, lose their tail and migrate through the blood stream and lungs reaching the liver. In the liver, schistosomes mature into male and female worms, which pair and release eggs in the mesenteric or bladder venules. Eggs released into the environment through the digestive or urinary tract hatch and infective miracidiae may infect snails, closing the cycle.

The majority of the human pathology from schistosomiasis occurs in high burden infections when the eggs are unable to exit from the human host, causing inflammatory responses, granulomas and fibrosis. These pathological changes are responsible for the long-term pathology such as portal hypertension and hepatosplenomegaly in the case of *S. mansoni*, and haematuria, urinary tract infections, hydronephrosis and kidney failure in *S. haematobium*. Inflammation of the female reproductive tract may cause cervical lesions that are risk factors for acquiring sexually transmitted diseases such as HIV [3].

Current treatment and control of schistosomiasis is dependent on solely one drug, praziquantel (40 mg/kg single dose). Cure rates with this single dose have been reported to vary between 40-90% [4, 5], but these depend largely on the timing after initial infection, on the pre-treatment parasite load and the intensity of reinfection [6, 7]. Repeated praziquantel dosing may thus be required to achieve full cure in those populations. However, mass treatment with this drug does not prevent reinfection and therefore in exposed populations the disease prevalence returns

to its original level within 6 to 8 months following chemotherapy. The development of a vaccine against schistosomiasis would be an essential tool in the control of this important parasitic disease.

Vaccination studies in mice and non-human primates with radiation-attenuated cercariae have provided the strongest proof-of-concept that vaccination against schistosomiasis is feasible [8, 9]. Antigens from stage-specific parasites have thus been identified as vaccine candidates, aiming to prevent infection or reduce worm burden. The pathway for WHO endorsement of these candidate vaccines would be to generate at least a 40% reduction in worm burdens ([http://who.int/immunization/research/meetings\\_workshops/Schistosomiasis\\_VaccineRD\\_Sept2014.pdf](http://who.int/immunization/research/meetings_workshops/Schistosomiasis_VaccineRD_Sept2014.pdf)).

Typically, these vaccine candidates are tested for proof-of-efficacy in large-scale Phase 2 and 3 field trials in *Schistosoma*-endemic areas, where the endpoint is usually the incidence of infection as detected by egg production, worm antigen or disease following natural infection. To obtain a good estimate of the effect size, trials of long duration and/or large population sizes are necessary. Conducting controlled, experimental infection studies has been shown to eliminate several drawbacks of the traditional proof-of-efficacy approach and has been well-established as a model for downselecting vaccine candidates for malaria, dengue and influenza [10].

In the first controlled human *Schistosoma mansoni* Infection (CoHSI) study that took place between 2016-2018, we successfully developed a male-only controlled human *Schistosoma mansoni* infection model (trial name: CoHSI1 study). In total 17 healthy volunteers were exposed to increasing doses of male cercariae. Controlled infection with 20 male *Schistosoma mansoni* cercariae was safe and well-tolerated, and had a high attack rate (82%) [11]. In analogy, this subsequent study aims to establish a female-only controlled human *Schistosoma mansoni* infection (CoHSI) model.

The sex of the worms has been hypothesised to differentially impact host immune responses. In contrast to males that trigger strong innate immune responses, females are found to dampen innate immune reactions resulting in improved parasite survival [12]. This makes female worms an important vaccine target. Not only would the establishment of a female-only CoHSI model allow exploration of sex-specific immune responses, but also it may be used to provide early proof-of-concept data on candidate schistosomiasis vaccines. This is of particular relevance as one of the developed schistosomiasis vaccine candidate's target antigens is preferentially expressed on female schistosomes.

## 2. OBJECTIVES

### Primary Objective:

- To investigate the safety, tolerability and attack rate of female *Schistosoma mansoni* cercariae in healthy Schistosoma-naïve volunteers

### Exploratory Objectives:

- To investigate the kinetics of circulating anodic antigen (CAA) after infection with female *Schistosoma mansoni* cercariae in healthy Schistosoma-naïve volunteers
- To investigate immunological, metabolic and microbiome changes after infection with *Schistosoma mansoni* female cercariae
- To explore potential differences in CAA kinetics and immunological responses after infection with male or female *Schistosoma mansoni* cercariae

### 3. STUDY DESIGN

This study is an open label, dose escalation intervention trial with an adaptive design.

Volunteers will be exposed to predefined doses of cercariae in groups of three and subsequently seven volunteers. Dose escalation will be performed according to the schedule depicted in figure 1. If all three volunteers in one group show detectable circulating anodic antigen in serum, seven additional volunteers will be exposed to the same dose. If not all volunteers in one dose group become infected, the next group of three volunteers will be exposed to a higher dose. The highest dose is 60 cercariae. If one or more volunteers from group A of 60 cercariae have a positive CAA test, another seven volunteers will also be exposed to this dose (group B). If both group A and group B volunteers (total 10) were exposed to the same dose, the study will stop.

[figure not shown]

Figure 1. Dose schedule. In case all volunteers become positive for *Schistosoma* circulating anodic antigen, the additional volunteers will be exposed to the same cercariae dose (green arrows, continue from group A to B). In case not all volunteers become positive for *Schistosoma* circulating anodic antigen, the dose will escalate (red or yellow arrows).

In the clinical study performed earlier we exposed four groups to male cercariae. The starting dose for the first group (A1) was also 10 cercariae. After dose-escalation to 30 cercariae for the second group (A2), we decided to dose de-escalate and expose the third group (A3) to 20 cercariae because of the burden of severe adverse events related to acute schistosomiasis syndrome in one of the volunteers (please refer to paragraph 11.3 or the Product Dossier section 2.3.2: Human exposure" for more information). The last cohort was then also exposed to 20 cercariae (B). We have thus adjusted the dose escalation schedule to allow for slower escalation if needed.

In addition, we have included cercarial doses that are higher than those used in the male cercariae infection study. This has been done for two reasons: 1) rodent experiments suggest that female cercariae may be less likely to establish infection as worm counts rendered fewer numbers in single-sex female infected animals when compared to single sex male infected animals; and 2) because female worms do not fully mature if they are unable to mate, CAA levels are expected to be lower than in mixed or single-sex male infections.

All volunteers included in the trial will be followed as out-patients for one year. They will be followed on a weekly basis starting at week 1 after infection until 16 weeks after infection. At week 18, 20 and one year after infection the final visits will take place. All volunteers will be treated with praziquantel (PZQ) 60 mg/kg at 8 weeks after infection and at 12 weeks after infection (Figure 2).

[figure not shown]

Figure 2. Trial schematic for CoHSI2 study

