#### 4.4 Sample size calculation

Subject to safety and tolerability we aim in these studies to achieve a 100% infection rate in 10 subjects. At a lower infection rate of 80% (for example) this sample size will estimate attack rate with precision of approximately  $\pm 22.5\%$ ; i.e. ruling out an attack rate of less than 50%. For future vaccine proof-of-concept efficacy studies, small groups of roughly 10 subjects are generally preferred, allowing for detection of roughly ~50% protective vaccines with a power of 80% ( $\alpha < 0.05$ , 2-tailed). A 100% attack rate in the infectivity control group (i.e. group exposed to pathogen, but not receiving the vaccine) is required to achieve this power. With a 80% attack rate and equal number of subjects ( $n=10$ ), the power to detect an estimated 50% efficacy is reduced to 63%. Therefore, we aim in this study to achieve a 100% attack rate in 10 subjects.

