### 9.5 Safety committee

For this study, a safety monitoring committee (SMC) will be appointed which will be independent of the investigators and sponsor and has no conflict of interest with the sponsor of the study. This SMC will consist of three experienced clinicians qualified to evaluate safety data from clinical studies with schistosome infections. Their main responsibility will be assessing safety reports or serious adverse events and advising the sponsor/investigator on trial continuation. Dose will be escalated 10 weeks after infection, i.e. 2 weeks after treatment, of a dose group, whereby <100% of volunteers were infected (showed detectable serum CAA). This can be a group of 3 or a group of 10 volunteers. The SMC can advise the sponsor of the trial not to escalate the dose, stop the trial, withdraw individual subjects or suspend further study procedures. Should the sponsor decide not to fully implement the advice of the SMC, the sponsor will send the advice to the reviewing METC, including a note to substantiate why (part of) the advice of the SMC will not be followed.

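### Expansion from group A to group B is triggered by the antigen result alone; the week-10 point and the safety committee's scheduled review cover dose escalation only

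*Protocol*

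**What the plan says.** Section 3 of the protocol gives two routes from group A (three volunteers) to group B (seven volunteers at the same dose). Below the top dose: "If all three volunteers in one group show detectable circulating anodic antigen in serum, seven additional volunteers will be exposed to the same dose". At the top dose: "If one or more volunteers from group A of 60 cercariae have a positive CAA test, another seven volunteers will also be exposed". The Figure 1 caption repeats the antigen-only rule for the move from A to B. Neither the text nor the caption attaches a safety condition to it.

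The Summary, under Intervention, puts it differently: "Depending on the outcome of infection and safety data, the dose will be escalated or additional volunteers will be exposed". The additional exposure meant there is at an unchanged dose. Section 4.4 also qualifies the aim: "Subject to safety and tolerability we aim in these studies to achieve a 100% infection rate in 10 subjects".

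Section 9.5 sets a time point for escalation: "Dose will be escalated 10 weeks after infection, i.e. 2 weeks after treatment, of a dose group" in which fewer than 100% of volunteers were infected. Section 13.2 has the SMC review all safety data ahead of a dose escalation, with the aim of an independent expert look before the trial proceeds. Section 9.5 describes the committee's general role: "Their main responsibility will be assessing safety reports or serious adverse events and advising the sponsor/investigator on trial continuation".

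**The concern.** The section that governs conduct omits a safety condition that the Summary promises, and the two scheduled safeguards elsewhere are attached to the other branch of the algorithm. As written, group B can be exposed once the antigen results are in, with no fixed waiting time and no scheduled independent review of how group A fared.

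A positive antigen result gives no safety clearance. Section 13.1 says that adverse events, acute schistosomiasis syndrome in particular, may be unrelated to antigen level, and for that reason relies on close clinical monitoring. Section 3 does not say that anyone reviews those clinical data before group B. Section 13.1 also states that controlled infection with female cercariae has not been done in humans before, and the volunteers gain no benefit from taking part (11.3).

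**Working it through.** No stated sample size, power or error rate depends on this point, so there is no figure of the plan's to reproduce. The check sets the sections side by side and adds simple arithmetic.

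**1. Which safety step applies to which branch**

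| Step | Trigger in section 3 | Week-10 point (9.5) | SMC review of all safety data (13.2) |
|---|---|---|---|
| Escalation to the next dose | not all of group A CAA-positive | yes | yes |
| Expansion below 60 cercariae | 3/3 CAA-positive | no: 9.5 is limited to groups below 100% infected | not named |
| Expansion at 60 cercariae | at least 1/3 CAA-positive | no: no higher dose exists | not named |

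Two cases follow. If 3/3 are positive at the starting dose of 10, no escalation has yet occurred. Section 3 ends the study once groups A and B have had the same dose, so the trial could complete without a scheduled SMC review. At 60 cercariae, the review before escalation covered lower doses; nothing schedules a review of the first three volunteers at 60 before seven more follow.

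**2. Timing**

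- Infection is assessed by serum CAA at week 8 (8.3, Safety laboratory evaluation).
- The first praziquantel dose is also given at week 8 (section 3).
- Acute schistosomiasis syndrome occurs three to ten weeks after infection (13.1).
- Largest possible gap: week 10 − week 8 = 2 weeks. Assay turnaround and scheduling may shorten it, and the protocol gives no lower bound.

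**3. Share of volunteers exposed at this step**

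7 / (3 + 7) = 70% of the final dose cohort.

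**4. What the discontinuation criteria in 8.7 would catch**

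The group A criterion is more than 1 of 3 volunteers with a related grade 3 event persisting at grade 3 for more than 48 hours. That means at least 2/3 = 66.7%. One volunteer is 1/3 = 33.3% and does not meet it. Yet section 3 reports that the team stepped down from 30 to 20 male cercariae "because of the burden of severe adverse events related to acute schistosomiasis syndrome in one of the volunteers", in a group that 11.3 gives as three.

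As an illustration, let q be the probability that a volunteer has such an event. Then P(at least 2 of 3) = 3q²(1 − q) + q³, and P(exactly 1 of 3) = 3q(1 − q)².

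| Assumed q | Count in 8.7 met | Exactly one affected, count not met |
|---|---|---|
| 2/11 | 116/1331 = 8.7% | 486/1331 = 36.5% |
| 1/3 | 7/27 = 25.9% | 12/27 = 44.4% |
| 1/2 | 50.0% | 37.5% |
| 2/3 | 74.1% | 22.2% |

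The value 2/11 is the proportion with severe events suggestive of the syndrome at 20 male cercariae (11.3); whether those events lasted more than 48 hours at grade 3 is not stated. The other values are assumptions. Over this range, a single affected volunteer in group A is a common outcome (22% to 44%), and the count in 8.7 does not act on it.

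**The case against.** The strongest reply is that section 3 sets out only the infection half of the algorithm. It words escalation on CAA alone as well, and leaves safety to other sections. The Summary and 4.4 state the safety condition; 9.1 obliges the sponsor to suspend if safety is at risk; 8.7 has a threshold specific to group A and also lists a single related serious adverse event and advice from the SMC or the investigator. The SMC may advise stopping or suspending at any time, and the purpose that 13.2 gives for its review could be read to cover expansion. Weekly visits with solicited symptoms cover weeks 3 to 8 of the risk window. Expansion repeats a dose already given, and the male study shows that the team does act on one volunteer's severe events.

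Much of this stands: oversight is not absent, and the finding should not be read that way. It does not close the gap. For escalation, 9.5 and 13.2 add a scheduled step to section 3; for expansion, no section does. The criteria in 8.7 permit discontinuation without requiring it, and a grade 3 event is not in itself a serious adverse event (9.2.2). The response in the male study was a judgement, whereas section 3 here says that the next seven will be exposed. Repeating a dose is limited reassurance when three volunteers are all the human experience at that dose and their risk window may still be open.

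Figure 1 is not shown, so a criterion in it cannot be excluded. The caption, however, gives the A-to-B arrow an antigen-only rule.

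**Conclusion.** The concern holds. Section 3 and the Figure 1 caption make same-dose expansion depend on CAA alone, the Summary adds safety data, and the week-10 point and SMC review are scheduled for escalation only. The step exposes 70% of the final dose cohort, up to two weeks before the stated syndrome window closes in group A.

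This should be changed, though it is not a failure of oversight as a whole. The harm avoided cannot be computed from the protocol. The comparison with the male study rests on the count alone: the protocol does not give that group's CAA results or say whether the severe events lasted more than 48 hours at grade 3. If a female group A repeated that picture with 3/3 CAA-positive, section 3 would send seven more volunteers to the same dose unless another criterion applied or someone used a general or discretionary power.

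**What to change.** State in sections 3, 9.5 and 13.2 that the SMC reviews all group A safety data through week 10 before either dose escalation or same-dose expansion, including expansion at 60 cercariae. Reword the expansion rules in section 3 and the Figure 1 caption so that, as in the Summary, both infection outcome and safety data decide the step.

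The cost is amendment wording in three sections and the caption, one more review by a committee that already exists, and a wait of at most about two weeks before group B.
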